#### Strain echocardiography

Echocardiography for the evaluation of LVH will take place during screening as well as at the end of the treatment phase. Doppler imaging or two-dimensional speckle tracking echocardiography is used to measure strain and strain rate. With these techniques subclinical heart disease in fibrotic processes can be detected, with the predominant planes of strain that are initially affected mirroring the histological location of early fibrosis [45, 46]. Global longitudinal strain is measured as percent and correlates well with myocardial fibrosis [47]. The physician performing the examination will be blinded to the patient’s treatment assignment.

#### Body composition monitoring

BCM will be performed during screening and will be repeated at 2-month intervals. BCM measurements are based on bioimpedance spectroscopy. The measurements are fed into a model to measure overhydration of an individual [41]. Fluid overload assessed by BCM is expressed as an absolute value in liters or as a relative value as a percent [48]. It is a reproducible body fluid volume determination over a wide range of body compositions at different states of health and disease [40]. Only patients who achieve their optimal dry weight at the end of dialysis treatment and tolerate it well will be enrolled in the study. Should patients present themselves with hypervolemia as measured by BCM during the treatment phase, the dry weight will be adapted dependent on BCM results in accordance with clinical judgment and standard of care equally in both treatment groups.

#### Lung ultrasound

The assessment of extravascular lung water will take place as part of the screening procedures with the help of lung ultrasound, which can visualize lung edema and classify it semiquantitatively [38, 39, 49]. Only patients without signs of pulmonary edema will be enrolled in the study.

#### Laboratory analyses

Biochemical data will be collected prior to hemodialysis at baseline and periodically (e.g., intact PTH, calcium, phosphate, 25(OH)D, 1,25(OH)_2_D every 2 weeks during the first 10 weeks followed by measurements every 4 weeks; while intact FGF23, s-Klotho and pre- and postdialysis TnT will be measured at 8-week intervals). Furthermore, proBNP levels will be measured as a marker of body fluid volume every 8 weeks. Additionally, an RAAS fingerprint will be conducted at the start and at the end of the treatment phase [25, 28, 29, 50]. The RAAS fingerprint is a mass spectrometry-based quantification of angiotensin metabolites, which will be performed by a resident diagnostic service provider (Attoquant Diagnostics). Serum samples will be used to measure the following parameters: Ang I, Ang II, Ang-(1–7), Ang-(1–5), Ang-(1–9) and aldosterone.

Intact PTH, calcium and phosphate will be analyzed in serum samples using the Cobas assay (Roche; reference ranges: PTH 15–65 pg/ml, calcium 2.15–2.55 mmol/l and phosphate 0.81–1.45 mmol/l). Vitamin D will be measured using serum samples chemiluminescent immunoassays (DiaSorin; reference ranges: 1,25-(OH)_2_D 19.9–79.3 pg/ml and 25(OH)D 75–250 nmol/l). Ionized calcium will be measured during every dialysis session (using blood gas analysis (ABL 800 Flex, Drott)). Intact FGF23 will be analyzed in plasma samples using chemiluminescent immunoassays (DiaSorin; reference range: 23.2–95.4 pg/ml). TnT and proBNP will be measured from serum samples using Cobas electrochemiluminescence immunoassays (Roche; reference ranges: TnT 0–14 ng/L and proBNP 0–125 pg/ml).

The timeline of the planned procedures, study visits and scheduled dose titrations is shown in Fig. 3.

**Fig. 3 Fig3:**
[figure not shown]
Study synopsis

### Investigational products

The pharmacodynamics of ETL and cinacalcet are similar. They both cause rapid, dose-dependent decreases in circulating levels of PTH, FGF23, calcium and phosphorus in CKD patients.

A single intravenous dose of ETL can lower serum levels of PTH for up to 72 h in patients on hemodialysis. FGF23 levels decrease by over 30% at 24 h after a single 10-mg dose of ETL, while little or no effect is shown on 1,25(OH)_2_D levels in a study conducted by Martin et al. [51]. The most frequent treatment-emergent adverse event is a decrease in blood calcium [52]. ETL dosage should be between 2.5 mg and 15 mg three times a week. The starting dose is 5 mg three times a week. To achieve a target value of PTH (100–300 pg/ml), the dosage will be adapted every 4 weeks in steps of 2.5 or 5 mg during the titration phase. Serum calcium will be measured at every dialysis session. Target levels of serum calcium corrected for serum albumin are ≥ 2.08 mmol/l.

ALFA is an analogue of vitamin D3. ALFA can decrease PTH levels by ≥ 30% and increase FGF23 levels threefold [53]. In general, ALFA is a safe and well-tolerated established treatment for sHPT.

The starting dose is 1 μg, administered as an intravenous bolus three times a week at the end of hemodialysis. ALFA dosage should be at least 0.5 μg three times a week with no maximal dose. Titration will be performed in 0.5- to 1-μg steps at 4-week intervals, depending on PTH values and serum calcium and phosphate levels. The target value of PTH is equivalent to the ETL group. Serum calcium corrected for serum albumin should be no higher than 2.55 mmol/l and serum phosphate levels should be below 2.5 mmol/l.

The goal is to achieve a similar reduction in PTH in both study groups while FGF23 is elevated in the ALFA arm and suppressed in the ETL arm in order to analyze the causality of FGF23 reduction on LVH and fibrosis.

However, it is likely that the levels of PTH will vary, simply due to the different pharmacodynamics of the two drugs. Even though the dose of the study medication can be changed during the drug titration period as well as later on when necessary in order to reach target PTH levels, these adaptations are often limited by serum calcium and phosphate levels.

#### Other HPT treatments

Cinacalcet treatment as well as oral and intravenous vitamin D therapy will be discontinued during the washout phase of 4 weeks. Phosphate binder therapy can be continued and will be adapted depending on serum electrolytes during the treatment phase. There are no restrictions on calcium supplements, the dialysate calcium concentration, or the type or dose of phosphate binders prescribed. Participants randomized to ETL can receive additional vitamin D analogs as a rescue therapy only when the investigator thinks that it is necessary to protect participant safety.

### Data Safety Monitoring Board

An independent Data Safety Monitoring Board of the Medical University of Vienna will be convened to assess the safety of treatment as well as the superiority of one treatment over the other [54, 55]. Interim analysis will be performed by the board after the completed follow-up of 10 cases in each treatment group (one-third of the planned study population). The Lan and DeMets alpha spending method using O’Brien–Fleming type boundaries will be applied and the trial will be stopped if *p* < 0.000207 [56].

### Quality control and quality assurance

The study monitor will contact and visit the investigator regularly and will be allowed, on request, to have access to all source documents needed to verify the entries in the electronic documentation and other study-related documents provided that subject confidentiality is maintained in agreement with local regulations. It will be the monitor’s responsibility to inspect the electronic case report forms at regular intervals throughout the study to verify the adherence to the study protocol and the completeness, consistency and accuracy of the data being entered. The monitoring standards require full verification for the presence of informed consent, adherence to the inclusion/exclusion criteria, documentation of serious adverse events (AEs)/serious adverse device effects and the recording of the main efficacy, safety, and tolerability endpoints. At least three monitoring visits are scheduled. The monitor will be working according to standard operating procedures and will provide a monitoring report after each visit for the sponsor and the investigator.

### Safety evaluation and reporting of adverse events

The investigators ensure that adequate medical care is provided in any clinical situation, including emergencies. All AEs observed by the investigator or reported by subjects are to be properly captured in the subjects’ medical records. This collection period will be from the time of the first dose of the investigational product to 30 days after the last dose.

It will be left to the investigator’s clinical judgment to determine whether an AE is related and of sufficient severity to require the subject’s removal from treatment. As defined by the International Conference on Harmonization guidelines and World Health Organization Good Clinical Practice guidelines, serious AEs are events that result in patient death, are life-threatening, require or prolong hospital stay, cause persistent or significant disability or incapacity, result in congenital anomaly or birth defect, or necessitate specific interventions. Events that are suspected unexpected serious adverse reactions (SUSARs) will be reported to the responsible ethics committee — the European Medicines Agency via the Clinical Trials Coordination Center of the Medical University of Vienna. Fatal SUSARs will be reported as soon as possible, but at the latest within 7 days and nonfatal SUSARs within 15 days.

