### Statistical methods

Data will be described as means and standard deviation or medians and interquartile range for continuous symmetric and skewed variables, respectively. Distributions of the analyzed parameters will be visualized by boxplots and histograms.

The primary endpoint (change in LVMI from baseline to 12 months) will be analyzed by the analysis of covariance. The main variable in the model to be tested will be treatment group, which represents the treatment effect on change in LVMI 1 year after baseline between the two treatments. Baseline LVMI for each patient will be used as a covariate in the model and the interaction between treatment group and baseline LVMI will be included. Furthermore, to account for stratification during randomization, the stratification factors will also be included in the model. The secondary endpoints (changes in FGF23, s-Klotho, PTH, 25(OH)D, 1,25(OH)_2_D, proBNP, pre- and postdialysis TnT and RAAS metabolites) will be analyzed analogously. All analyses will be conducted according to the intention-to-treat principle. Two-sided *p* values lower than 0.05 will indicate statistical significance.

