### Sample size calculation

On the assumption, based on published data, that the mean LVM/BSA of hemodialysis patients determined by cMRI is 100 g/m^2^ with a standard deviation of 25 g/m^2^ [42] and an expected treatment effect of delta LVMI of 20 g/m^2^, 25 patients are needed per group to detect this difference with 80% power using a two-sample *t* test at an alpha level of 0.05. Assuming 10% attrition (drop out/loss to follow-up) within 1 year of follow-up, the final sample size in the intention-to-treat analysis will be 31 patients.

Patients receiving a renal transplant as well as those who become pregnant (which is unlikely due to the significantly reduced fertility of women under dialysis) will drop out of the study.

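### Adverse-event collection ends 30 days after each patient's last dose, so deaths and serious events in patients who stop study drug early are not covered from then to month 12

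*Protocol article*

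**What the plan says.** All points here are in the protocol article.

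- **Safety evaluation and reporting of adverse events, scope.** "All AEs observed by the investigator or reported by subjects are to be properly captured in the subjects’ medical records". The end of collection is set in the next sentence: "This collection period will be from the time of the first dose of the investigational product to 30 days after the last dose".
- **Same section, removal from treatment.** The investigator's clinical judgment is used "to determine whether an AE is related and of sufficient severity to require the subject’s removal from treatment".
- **Same section, seriousness.** The definition is taken from guidelines: "serious AEs are events that result in patient death, are life-threatening, require or prolong hospital stay", followed by further categories. The collection window is not varied for any of them.
- **Treatment phase.** Treatment is planned for 12 months.
- **Data Safety Monitoring Board.** The board is to judge treatment safety as well as superiority, with an interim look once 10 patients per group have finished follow-up.
- **Statistical methods.** "All analyses will be conducted according to the intention-to-treat principle". The analyses described there are analyses of covariance of change in LVMI and in biomarkers. No analysis of deaths or serious events is described.
- **Sample size calculation.** Attrition of 10% within the year is assumed. Patients who receive a transplant or become pregnant leave the study.

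**The concern.** The window is anchored to each patient's own last dose, whereas the arms are formed at randomisation and treatment is planned for a year. In a patient who stops early, a death or a heart-failure admission more than 30 days later falls outside the stated collection period.

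Three features of this trial make that matter more than it would elsewhere:

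- **A safety event can close the safety window.** An adverse event may lead to removal from treatment, and collection then ends 30 days after the last dose.
- **The drugs are limited by different effects.** Under Investigational products, low blood calcium is the commonest adverse event on etelcalcetide, while alfacalcidol titration is bounded by upper limits for calcium and phosphate. The timing of stops could therefore differ by arm. The trial is single-blinded, and under Outcome measurements the only staff described as blinded are the radiologist reading the cMRI and the physician performing echocardiography. Decisions to stop may thus be made with knowledge of the arm.
- **The population is at high risk.** The Background and the Discussion both stress cardiac death and mortality in dialysis patients.

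At stake is whether the board and the final report can compare serious harms between arms over equal time. With 62 patients, one or two unrecorded deaths could change the safety picture.

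**Working it through.** The article gives no figure for this point, so there is none to reproduce. The check is the length of time that the stated window leaves uncovered.

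**Inputs from the article**
- Planned treatment: 12 months (Treatment phase).
- End of collection: 30 days after the last dose (Safety evaluation and reporting of adverse events).
- Randomised patients: 62 (Abstract; Study design).
- Attrition: 10% in the year (Sample size calculation). This counts drop-out and loss to follow-up, not stops of study drug.

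**Assumptions, not in the article**
- First dose close to randomisation, so month 12 is the same point for both.
- For the total only: early stops spread evenly over the year.
- The proportion stopping early is varied from 5% to 30%.

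**Step 1: one patient.** 30 days is 30/30.4375 = 0.986 month. For a last dose at month m:

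uncovered months = 12 − m − 0.986, and not less than 0.

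- m = 1: 10.0 months
- m = 3: 8.0 months
- m = 6: 5.0 months
- m = 9: 2.0 months
- m = 11: 0.0 months
- Completer (m = 12): 0; collection runs to about month 13.

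**Step 2: average per early stopper.** The longest possible gap is L = 12 − 0.986 = 11.014 months. With stops uniform over 12 months the mean gap is

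L² / (2 × 12) = 11.014² / 24 = 5.05 months.

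**Step 3: whole trial.** Planned observation is 62 × 12 = 744 patient-months. Uncovered time is 62 × (proportion stopping early) × 5.05:

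- 5% (3.1 patients): about 16 patient-months, 2.1%
- 10% (6.2 patients): about 31 patient-months, 4.2%
- 20% (12.4 patients): about 63 patient-months, 8.4%
- 30% (18.6 patients): about 94 patient-months, 12.6%

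**Step 4: what cannot be computed.** The article gives no rate of death or serious events and no stopping rate by arm. Neither the number of missed events nor the difference in coverage between arms can be derived.

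**Step 5: with the fix.** If deaths and serious events are collected at least to month 12 for every randomised patient, the uncovered time within the year is 0 whatever the date of the last dose.

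**The case against.** A window of 30 days after the last dose is a common rule for adverse-event reporting, and it loses nothing for completers. The event that causes a stop normally falls inside it. Unequal observation time can be handled with exposure-adjusted rates, and the tabulation of safety data belongs to an analysis plan that is not shown. The link from calcium and phosphate limits to unequal stopping is an inference, because Investigational products discusses them as limits on dose adaptation, not as causes of permanent discontinuation. All of this is fair. It shows that the gap is confined to early stoppers and that differential stopping is a possibility only. It does not close the gap: exposure-adjusted rates describe risk while observed and cannot recover events that were never collected.

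Three stronger readings are tempting, and the article does not support them.

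- **That the window contradicts the intention-to-treat statement.** That sentence closes a paragraph on LVMI and biomarkers. Neither death nor a serious adverse event is an endpoint, and no between-arm analysis of deaths is proposed.
- **That later deaths are lost, or that a 12-month comparison of them is impossible.** The rule closes adverse-event collection; it does not say that follow-up or vital-status ascertainment ends, and the sentences on suspected unexpected serious adverse reactions carry no end date. A patient kept to the 12-month cMRI would be known to be alive. Non-fatal serious events in such a patient would still lie outside the stated window.
- **That a birth defect, listed as serious, could hardly be captured.** The category is part of a guideline definition of seriousness. Pregnancy is excluded at entry and called unlikely later, and pregnancy follow-up is a matter that a condensed article may leave to the full protocol.

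**Conclusion.** The point holds as a gap in safety collection. The article states the window outright, without exception for deaths or serious events, so this is a criticism of a rule that is fixed in the text and not of something left out.

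For the individual early stopper the gap is large: about 8 months for a last dose at month 3 and 5 months at month 6. For the trial as a whole it is probably modest: about 31 of 744 patient-months (4.2%) at 10% early stopping, with a range of 2.1% to 12.6% for 5% to 30%. These totals rest on the assumed proportions and on even spread of stops. The 10% borrows the article's attrition figure, which measures something else.

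A reader might go further, assume very different stopping rates in the two arms and derive a percentage by which one arm's events would be under-recorded. The article gives no stopping rate by arm, so any such figure would only restate the assumption. What can be said is that the treatment itself can shorten observation, and that coverage may therefore differ by arm by an unknown amount. The primary LVMI analysis is not affected.

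**What to change.** Amend the section on safety evaluation so that deaths and serious adverse events are collected for every randomised patient until 12 months after randomisation or 30 days after the last dose, whichever is later. This includes patients who stop study drug or leave the study, subject to their consent. Keep the present 30-day rule for non-serious events. Report on-treatment events in a separate table, so that events long after the last dose do not blur the drug-related profile.

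The cost is an amendment, consent for patients who have left, and a record check for those off study drug. For patients still dialysing at the two recruiting centres this is mainly a review of existing records, without added procedures; for transplanted patients it may take a further enquiry. Some recorded events will be unrelated to the drug, which the on-treatment table separates. By the article's Trial status section, recruitment began in October 2017 and enrolment was expected to be complete in November 2019, so for patients who have already left, coverage would depend on what consent and records allow.

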### Statistical methods

Data will be described as means and standard deviation or medians and interquartile range for continuous symmetric and skewed variables, respectively. Distributions of the analyzed parameters will be visualized by boxplots and histograms.

The primary endpoint (change in LVMI from baseline to 12 months) will be analyzed by the analysis of covariance. The main variable in the model to be tested will be treatment group, which represents the treatment effect on change in LVMI 1 year after baseline between the two treatments. Baseline LVMI for each patient will be used as a covariate in the model and the interaction between treatment group and baseline LVMI will be included. Furthermore, to account for stratification during randomization, the stratification factors will also be included in the model. The secondary endpoints (changes in FGF23, s-Klotho, PTH, 25(OH)D, 1,25(OH)_2_D, proBNP, pre- and postdialysis TnT and RAAS metabolites) will be analyzed analogously. All analyses will be conducted according to the intention-to-treat principle. Two-sided *p* values lower than 0.05 will indicate statistical significance.

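### The primary ANCOVA tests the treatment term alongside a treatment-by-baseline-LVMI interaction without saying at which baseline LVMI the effect is read

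*Protocol article*

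**What the plan says.** All of the analysis text is in the protocol article, Statistical methods:

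- Method: "The primary endpoint (change in LVMI from baseline to 12 months) will be analyzed by the analysis of covariance".
- Tested term and its meaning: "The main variable in the model to be tested will be treatment group, which represents the treatment effect on change in LVMI".
- Baseline LVMI is a covariate, and "the interaction between treatment group and baseline LVMI will be included".
- Strata: "to account for stratification during randomization, the stratification factors will also be included in the model". Under Screening, washout phase and randomization these are urine volume (below 500 ml per day versus 500 ml or more) and centre.
- Secondary endpoints, from FGF23 to the RAAS markers: "RAAS metabolites) will be analyzed analogously".
- Significance: "Two-sided *p* values lower than 0.05 will indicate statistical significance".

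The section gives no centring of baseline LVMI, no coding of treatment and no baseline value for the contrast.

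Sample size calculation uses a plain two-sample t test. LVMI "determined by cMRI is 100 g/m^2^ with a standard deviation of 25 g/m^2" is assumed, with an "expected treatment effect of delta LVMI of 20 g/m^2". It arrives at 25 patients per group for 80% power and a final 31 per group (62 in total).

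**The concern.** Once a treatment-by-baseline interaction is in the model, the treatment effect is a line over baseline LVMI and no longer a single number. The treatment term on its own is the height of that line where the covariate equals zero. If the covariate is LVMI in g/m², zero is a heart without mass. If the covariate has been centred, zero is the average patient. Coding treatment 0/1 or −1/+1 makes no difference to the test, and a type III test of the term addresses the same hypothesis.

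The protocol says that the term represents the treatment effect, and it sizes the trial for a mean difference. Both are right only if baseline is centred or the contrast is taken at a stated typical baseline. Otherwise the primary p value belongs to a quantity of no clinical interest with a very large standard error, and a real 20 g/m² effect would usually be reported as non-significant.

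**Working it through.** **Inputs.** From Sample size calculation: mean LVMI 100 g/m², SD 25, effect 20 g/m², two-sided alpha 0.05, 25 per group, 31 per group after allowance for attrition. I also use 28 per arm, since 31 × 0.9 = 27.9. Assumptions: the planning mean and SD describe baseline LVMI, and the residual SD of change is 25, as in the planning t test. Both are varied below.

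**The plan's own figure.** n per group = 2 × (1.960 + 0.842)² × 25² / 20² = 24.5, so 25. Power at 25 per group is 80.7% by the normal approximation and 79.1% by the exact t calculation. The stated figure reproduces, and it refers to an average effect.

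**The tested term with baseline in g/m².** The treatment coefficient is the difference between two arm-specific intercepts. Leaving the strata aside, each intercept has variance s²/n × (1 + mean²/SD²), so

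SE = s × √(2/n) × √(1 + mean²/SD²).

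- Distance of LVMI = 0 from the mean: 100/25 = 4 SD.
- Inflation: √(1 + 100²/25²) = √17 = 4.12.
- At n = 25, s = 25: 25 × √(2/25) = 7.07, and 7.07 × 4.12 = 29.2.
- Noncentrality: 20/29.2 = 0.69. With 2 × 25 − 6 = 44 degrees of freedom, power is 10.3%.

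**Comparison by simulation** (4,000 trials per row, constant true effect of 20 g/m², residual SD 25, two binary strata in the model):

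| Per arm | Uncentred, formula | Uncentred, simulated | Centred, interaction kept | Interaction dropped |
|---|---|---|---|---|
| 25 | 10.3% | 9.8% | 77.0% | 77.2% |
| 28 | 11.0% | 10.6% | 82.9% | 82.8% |
| 31 | 11.7% | 10.1% | 85.6% | 85.6% |

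**Sensitivity of the uncentred test at 25 per arm (formula).**

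- Residual SD 20, 15, 10: power 13%, 20%, 39%.
- Baseline SD 20 or 15 with residual SD 25: inflation 5.10 or 6.74, power 8% or 7%.

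**If the effect varies with baseline (illustrative).**

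- A reduction of 20% of baseline mass is 20 g/m² at LVMI 100 and 0 at LVMI 0. The uncentred test then rejects in about 5% of trials, its nominal level, against 76% when centred (25 per arm).
- With no effect at the mean but a slope difference of 0.2, the difference at LVMI 0 is 0.2 × 100 = 20 g/m². The uncentred test then rejects about 10% of the time, by the calculation above, although the average effect is null.

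**The case against.** The strongest reply is that the protocol never says baseline is uncentred, nor that a raw coefficient is tested. Its wording points the other way: the term is described as the treatment effect between the two groups, and the sample size is for a mean difference. With a mean-centred covariate, or an adjusted mean difference at mean baseline, the same model delivers exactly that. ANCOVA with a treatment-by-centred-baseline interaction is an accepted analysis, and centring is a detail that an SAP, not shown here, could fix.

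Much of this stands. A reader might infer that the primary analysis has about 10% power, or that the plan enters baseline uncentred. The document supports neither as a fact. The 10% needs the uncentred reading and a residual SD near 25. Including the interaction is not itself an error, and dropping it is only one of two equivalent remedies.

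Nor can the factor of 4.1 be carried over to the secondary endpoints. It depends on each marker's own baseline mean and SD, which the document does not give. For a skewed marker with SD equal to its mean (an assumption), the inflation would be √(1 + 1) = 1.4.

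The appeal to the SAP does not stand in full. The protocol did not leave the model open. It chose the interaction, named the tested term and gave that term an interpretation which fails when the model is run with baseline in its natural units.

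**Conclusion.** The point holds as a badly fixed primary test. The model, the tested term and the claimed meaning of that term agree only under a condition that the protocol does not state. If baseline LVMI is centred or the contrast is taken at mean baseline, the plan does what it intends. If baseline is entered in g/m², the test concerns LVMI = 0, the standard error is about 4.1 times larger, and power falls from the planned 80% to about 10–12%. These figures rest on the planning mean and SD applying at baseline, a constant effect of 20 g/m² and a residual SD of 25. A smaller residual SD softens the loss without removing it.

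The choice decides the result. In simulated trials with a true 20 g/m² effect, 25 per arm and assumed baseline-to-12-month correlations from 0 to 0.8, the centred and uncentred tests of the same data disagreed on significance in 70–82% of trials. A primary p value that turns on such a software choice is not prespecified.

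**What to change.** State one of the following for the primary analysis:

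1. Change in LVMI modelled on treatment, baseline LVMI, urine-volume stratum and centre, with the treatment-by-baseline interaction reported as a supportive analysis.
2. The interaction kept, baseline LVMI centred at the overall mean of both arms, and the primary test defined as the adjusted group difference at mean baseline LVMI.

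In the simulations the two give practically the same power, so either will do. Apply the same rule to each secondary endpoint analysed in the same way, using that marker's own baseline.

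The cost is one sentence in the protocol or SAP, recorded before those who choose the model see results by arm. It changes nothing for patients, data collection or sample size. If an SAP already contains the rule, a cross-reference is enough.
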